# Association Between Household Livestock Ownership and Stunting in Children Younger Than 5 Years in Central Rural India: Protocol for a Case-Control Study

**DOI:** 10.2196/66576

**Published:** 2025-09-11

**Keywords:** stunting, wasting, livestock, tropical livestock unit, TLU, India, animal-source food, study protocol, case-control study

## Abstract

**Background:**

In resource-constrained environments where malnutrition in children is common, people coexist closely with livestock. Undernutrition, which can result in stunting, wasting, and being underweight, is still a major public health issue for children in India. Livestock serves as a direct source of protein through animal-source foods such as meat, milk, and eggs, which significantly reduce undernutrition in children younger than 5 years. The association between livestock ownership and stunting in children has not been explored well in Maharashtra, India.

**Objective:**

This study evaluates the relationship between stunting among children younger than 5 years in central India and livestock ownership by using the Tropical Livestock Unit (TLU) score.

**Methods:**

A community-based, case-control study will be conducted for 12 months among 614 children aged 6-59 months in a few rural blocks of Wardha district, Maharashtra. A predesigned semistructured questionnaire will collect data from the informant (either parent). Anthropometric measurements will be plotted on World Health Organization (WHO) standard growth charts for *z* scores for stunting and wasting. TLU will be used to represent the livestock count of all species. The categorical variables (stunted and nonstunted) will be analyzed using the Fisher exact test to find significant associations between different risk factors. All confounding variables will be analyzed using multivariable logistic regression. Associated risks will be identified and tabulated using the odds ratio with confidence intervals.

**Results:**

This study protocol will provide a comprehensive understanding of the associations of livestock ownership with childhood stunting and wasting among children aged 6-59 months in central rural India. This study will be conducted from October 2025 to September 2026. Currently, necessary approvals are obtained, and data collection is planned to begin from November 2025 to May 2026.

**Conclusions:**

Our findings will show the prevalence of the current stunting, wasting, and underweight rates among Indian children younger than 5 years and the association of these rates with livestock ownership by using the TLU index. These results will be instrumental in building new public health policies, integrated programs, and nutritional interventions.

**Trial Registration:**

Clinical Trials Registry – India CTRI/2024/05/066865; https://tinyurl.com/y3zvh5t7

**International Registered Report Identifier (IRRID):**

PRR1-10.2196/66576

## Introduction

Stunting, which refers to low height/length for age, is usually a result of chronic undernutrition, often linked to poor socioeconomic conditions, maternal health, infant care, and children’s nutrition. It restricts children from achieving maximum physical and cognitive capabilities [1]. In 2022, 149 million children younger than 5 years experienced stunted growth, which accounts for 22.3% of all children younger than 5 years globally [2]. More than a million child deaths are estimated annually due to stunting, which is defined as a height-for-age below minus 2 *z* scores of the median height-for-age in the World Health Organization (WHO) child growth standards [3]. Stunting and undernutrition continue to have a high prevalence globally.

In India, although there has been economic growth and significant decreases in child mortality rates, undernutrition and stunting are still prevalent [4]. For children, stunting, wasting, and underweight are crucial markers of their nutritional condition. Although wasting results from acute food scarcity and illness, stunting is due to recurring illnesses and long-term inadequate nutritional intake. Stunting has generally irreversible impacts on delayed motor development and decreased cognitive development. However, wasting is a major indicator of death and needs to be addressed right now. Underweight integrates weight for length/height and linear growth hindrance data [1].

One of the key priorities for the 2030 “Zero Hunger” Sustainable Development Goal is reducing stunting [5]. Stunting and wasting are also highlighted in the Global Hunger Index 2017 report, in which India ranked 100th [6]. The latest National Family Health Survey-5 (NFHS-5) was conducted in India from 2019 to 2021, which revealed that underweight, wasting, and stunting are common in Indian children younger than 5 years. The prevalence of underweight, wasting, and stunting according to NFHS-5 was 35.5%, 19.3%, and 32.1%, respectively [7]. This is undoubtedly lesser than that reported in the NFHS-4 study, which was performed between 2015 and 2016 [8]. The stunting and wasting rate for Maharashtra as per recent NFHS-5 (2019-2021) was 35.2% and 25.6%, respectively. As per NFHS-4 (2019-20) from the district fact sheet of Wardha, Maharashtra, the stunting rate for rural children younger than 5 years was 29.4%, and the wasting rate was 25.8% [9].

Agriculture, with its allied sectors such as animal husbandry and livestock production, is India’s largest source of livelihood [10]. One integrated agricultural component that enhances household income, consumption, productivity, and food security is livestock [11]. Livestock provides protein directly through meat, milk, and eggs, known as animal-source food or indirectly by boosting the household income for food purchases [12]. Livestock ownership can improve the nutritional diversity and the quality of nutrition for households that own them, even though it may also raise the risk of environmental enteropathy, a condition linked to the loss of nutrients in the stomach, in children [13]. The Wardha district in Maharashtra is notable for its livestock and poultry farming, which is essential to the rural economy. According to the 20th livestock census, Wardha district recorded 489,836 animals, of which 344,875 are poultry and cattle units [14]. A few studies conducted in African nations have shown that owning more livestock can greatly boost the consumption of food items derived from animals and enhance nutritional outcomes [15,16]. Nonetheless, few studies [4,17] have been conducted in India to examine the relations between household livestock ownership and the stunting and nutritional status of children younger than 5 years. The tropical livestock unit (TLU), an index used in this study, is created by giving each animal a weight and merging all of the livestock characteristics for the household into a single variable [18]. Additionally, a dearth of studies [19] in Maharashtra examines the association between livestock ownership and stunting in children younger than 5 years. This study seeks to evaluate the relationship between stunting among children younger than 5 years in central rural India and livestock ownership by using the TLU index, considering existing research gaps.

## Methods

### Study Design, Participants, and Setting

This case-control study will be conducted in a community-based setting. It will be performed for 24 months in a few randomly selected villages from 8 rural blocks of Wardha district, located in central Maharashtra, by using a computerized method. Cases and controls will be proportionally allocated based on the number of children younger than 5 years and the stunting prevalence in each block. Permission for the interviews will be obtained from the authority/sarpanch of the respective villages. The list of children younger than 5 years of the selected blocks will be acquired from the respective Anganwadi Center of the village. For each case, 1 control will be recruited through simple random sampling. Informants will be briefed on the study’s process and purpose. Participation will only be allowed after either parent gives written and informed consent. Data will be gathered using a semistructured questionnaire in English/Marathi via interviews. The questionnaire was developed and reviewed by field experts and will be validated through a pilot study (Multimedia Appendix 1). An infantometer/stadiometer will be used by the investigator to measure the length/height (in centimeters), and weighing scales will be used to measure the weight (in kilograms) of each child. The children’s height and weight measurements will be compared to WHO 2006 standards based on age and gender to calculate the height-for-age *z* score and weight-for-height *z* score. Stunting and wasting are defined as falling below –2 SD of the WHO reference median. After plotting the measurements on the WHO growth charts, stunted and nonstunted children will be listed separately. All stunted children will be the cases in this study, and all nonstunted children will be the controls.

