### Sample Size

The study will involve participants chosen based on specific inclusion and exclusion criteria. It will include all children younger than 5 years from the respective villages. Considering the overall number of children younger than 5 years in the Wardha rural area sample, the total population was 88,224 children [20].

Estimated sample size = n≥(NZ_(1-α⁄2)^2 p(1-p))/(d^2 (N-1)+Z_(1-α⁄2)^2 p(1-p)), where α (a)=.05; estimated proportion of children younger than 5 years who are stunted (height-for-age) *P*=.28 [9]; and estimation error (d) = 5% = 0.05. The minimal sample size calculated for this study will be 614, of which 307 are cases and 307 are controls, considering the ratio of case-control is 1:1.

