### Data Analysis

All the results will be calculated using RStudio software (version 4.3.2; Posit). The complete analysis dataset will consist of all study participants who have no missing data for any of the variables in the dataset. The study participants will be those individuals who meet the criteria for inclusion and exclusion. Baseline characteristics will be utilized to compile all the data, representing demographic variables with mean and standard deviation for continuous data and frequency and percentage for categorical data. The results will be examined for continuous data, which will be described using the minimum, maximum, average, standard deviation, standard error, and 95% CI for parametric data. The normality of the continuous outcome variables will be assessed initially with the Kolmogorov-Smirnov test at a 5% significance level (*P*≤.05). If the data are not rejected, a nonparametric test will be used to determine significance; otherwise, it will be considered normal. The significant difference at the 5% level (*P*≤.05) between stunted and nonstunted comparative groups will be determined using a 2-sided *t* test. Nonnormal data will be summarized using mean, median, and lower and upper quartiles for nonparametric testing and will be assessed for significance using the Mann-Whitney test. Categorical variables will be presented with frequency (n) and percentage value (%). The categorical variables (stunted and nonstunted) will be analyzed by Fisher exact test to find significant associations of different risk factors. All confounding variables will be analyzed using multivariable logistic regression. Associated risks will be investigated and tabulated using the odds ratio with a confidence interval. To understand the effects of multiple factors, confounding variables will be recognized and adjusted to understand the multiple factors that can influence the outcome (stunting). For the confounding effect, multivariable methods will be employed to estimate the association between exposure (livestock) and outcome (stunting), or the impact of one or more confounding factors such as WASH; wealth index of the household; episodes of illness; dietary habits; knowledge, attitude, and practices regarding livestock; and livestock diseases will be considered. Essentially, multivariable logistic regression will allow assessing the independent effect of each of the exposures.

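### The named analyses treat children as independent and leave out block and village, although children are sampled by block and village; the error in the confidence interval can go either way, depending on how controls are drawn

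*Protocol article*

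**What the plan says.** **Sampling** (Protocol article, Study Design, Participants, and Setting). Children come from "a few randomly selected villages from 8 rural blocks of Wardha district". On allocation: "Cases and controls will be proportionally allocated based on the number of children younger than 5 years and the stunting prevalence in each block". On controls: "For each case, 1 control will be recruited through simple random sampling". The text does not say whether that random draw is made within a village, within a block or across the whole study area. The Data Collection section repeats the random selection of villages and the use of village child lists. The number of villages is not given.

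**Exposure** (Introduction). The livestock index works by "merging all of the livestock characteristics for the household into a single variable", so it is fixed at household level.

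**Who enters** (Sample Size). "It will include all children younger than 5 years from the respective villages". The eligibility criteria set no limit of one child per household.

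**Analysis** (Data Analysis). Two-group comparisons use the t test, Mann-Whitney test or Fisher exact test. For adjustment: "All confounding variables will be analyzed using multivariable logistic regression". The named confounders cover hygiene, wealth, illness, diet, livestock practices and livestock disease. They are given as examples and do not include block or village. No random effect, conditional model or clustered variance is mentioned.

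**Sample size** (Sample Size). A single-proportion formula for a simple random sample, with no design effect.

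**The concern.** The sampling has a structure that the analysis does not use. With 614 children from a few villages, each village contributes many children, and those children share local livestock practice, water supply, sanitation and services. Two things follow.

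1. **Precision.** If livestock ownership and stunting both vary between villages, the model's standard error for the odds ratio is not the true one, and neither the confidence interval nor the P value has its stated meaning.
2. **Bias.** Recruitment numbers depend on block stunting prevalence. If the ratio of cases to controls then differs between blocks, and livestock ownership also differs between blocks, leaving block out shifts the odds ratio.

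The Conclusions section says the association is to guide policy, including the promotion of livestock ownership. The odds ratio and its interval should therefore reflect how the children were sampled.

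**Working it through.** **1. The plan's own figure.** Inputs from Sample Size: N = 88,224, p = 0.28, d = 0.05, Z = 1.96.

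Z²p(1−p) = 3.8416 × 0.2016 = 0.77447.

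n = 88,224 × 0.77447 / (0.0025 × 88,223 + 0.77447) = 68,326.5 / 221.33 = 308.7, rounded up to 309.

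This is within 2 of the stated 307 per group; twice 309 is 618, against the stated 614. The plan's figure is thus approximately reproduced, and it contains no allowance for clustering.

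**2. Children per village (assumed counts).** 614/16 = 38.4 and 614/40 = 15.35.

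**3. Ordinary design effect, for a proportion or mean.** DEFF = 1 + (m − 1) × ICC, with ICC assumed 0.01 to 0.05.
- 40 villages, ICC 0.01: 1 + 14.35 × 0.01 = 1.14; effective N = 614/1.14, about 537.
- 16 villages, ICC 0.05: 1 + 37.4 × 0.05 = 2.87; effective N = 614/2.87, about 214.

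**4. The odds ratio.** When controls are not balanced by village, the variance inflation is about 1 + (m − 1) × ICC(exposure) × ICC(stunting). With assumed exposure ICC 0.05 to 0.30 and stunting ICC 0.02 to 0.10:
- 40 villages, lowest values: 1 + 14.35 × 0.05 × 0.02 = 1.01 (SE × 1.01).
- 16 villages, highest values: 1 + 37.4 × 0.30 × 0.10 = 2.12 (SE × 1.46).

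For illustration, with an odds ratio of 1.5, 50% ownership and 307 per group, power is 70% without inflation, 62% at inflation 1.2, 53% at 1.5 and 43% at 1.95.

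**5. Simulation under a true odds ratio of 1.** 307 cases, 307 controls, 28% stunting, 16, 24 or 40 villages in 8 blocks, 2,000 runs per setting, unadjusted two-sided 5% test. Assumed between-village SDs on the logit scale for exposure and stunting: moderate 0.6 and 0.4, strong 0.9 and 0.6. The mean model SE was 0.162 throughout.

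| How controls are drawn | Type I error, moderate | Type I error, strong | True SD of log OR |
|---|---|---|---|
| At random across villages | 5.0–6.0% | 7.0–10.5% | 0.161–0.200 |
| Balanced to cases by block | 4.8–5.0% | 6.4–7.4% | 0.161–0.179 |
| Balanced to cases within village | 3.6–3.9% | 3.2–3.7% | 0.150–0.155 |

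Monte Carlo error at 5% is about ±1 percentage point (1.96 × √(0.05 × 0.95/2,000) = 0.0096), so the moderate results in the first two rows are close to nominal. In the worst setting the true SD exceeds the model SE by 0.200/0.162 = 1.23. With village balance it falls below it (0.150/0.162 = 0.93).

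**6. Block as a confounder.** 24 villages, village SDs 0.4 and 0.3, plus a block effect shared by exposure and stunting with SDs 0.5 and 0.4 (all assumed).
- Controls not balanced by block: mean log OR +0.158, that is exp(0.158) = 1.17 when the truth is 1; type I error 17.7%.
- Controls balanced to cases by block: mean log OR +0.003; type I error 4.4%.

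**7. Siblings alone.** With 10–30% of children in sibling pairs and a sibling stunting ICC of 0.1–0.3 (assumed), variance inflation is 1.01 to 1.09.

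**The case against.** **Clustering methods can be left to a fuller analysis plan, and the confounder list is open.** This is partly fair, since a condensed article need not describe every variance estimator. But the Data Analysis section is detailed: it fixes the software, the normality test, the analysis set, each two-group test and the model. Those two-group tests assume independent children, and the sampling section describes children who are not independent. An open confounder list could admit block, but it does not supply a clustered variance.

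**A reader might infer that the intervals are certainly too narrow.** The documents do not support this. It is the likely direction if controls are drawn at random across villages, which is the plainest reading. Even then the inflation is slight with moderate heterogeneity, and the direction reverses if controls are balanced within village.

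**A reader might infer that omitting block certainly biases the odds ratio.** This also goes too far. The allocation sentence covers cases and controls together, and the ratio is 1:1. If both follow the same block allocation, the bias almost disappears. The text does not say whether they do.

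**A reader might infer that siblings are enrolled.** Nothing rules this out, and all children under 5 in the villages are said to be included. However, the Data Collection section speaks of selecting children from the list, and no sentence states that siblings enter. Their effect alone would be small.

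What stands against the point is its uncertain size and direction; the mismatch between sampling and analysis remains.

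**Conclusion.** The point holds in this form: the analyses named do not match the block and village sampling, so the standard error of the livestock odds ratio can be wrong in either direction. Under the assumed village counts and heterogeneity, the type I error of a nominal 5% test runs from 3.2% to 10.5%. Block confounding is a separate, conditional risk: material if controls do not share the cases' block distribution (17.7% type I error in the one setting tried), negligible if they do.

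All of these magnitudes rest on assumed village counts, intracluster correlations, heterogeneity and sibling shares, because the documents give none of them. The odds-ratio results in the simulation are for an unadjusted comparison; adjustment for household covariates that vary by village could absorb part of the effect. The plan should be changed, but the documents do not show that the main result would be invalid.

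**What to change.** 1. State whether controls are drawn within village, within block or across the study area, and whether they follow the same block allocation as cases.
2. Include block as a fixed effect in the primary logistic model.
3. Account for village by a random intercept, or by conditional logistic regression stratified by village if controls are drawn within village.
4. If more than one child per household is enrolled, use cluster-robust standard errors.
5. Retain non-identifying block, village and household codes. The Ethical Considerations section promises full anonymisation, so these codes should be arranged before data collection, which is planned from November 2025.
6. Present the crude Fisher, t and Mann-Whitney results as descriptive.

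**Cost.** Mostly wording in the sampling and analysis sections, plus three code fields in the dataset. Recruitment numbers need not change. The intervals may become slightly wider.

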### Ethical Considerations

This study received approval on January 31, 2024, from the Institutional Ethics Committee of Datta Meghe Institute of Higher Education and Research (DMIHER(DU)/IEC/2024/137) to ensure adherence to ethical guidelines, respect participant rights, and meet established standards. This study has been registered with the Clinical Trials Registry-India under registration CTRI/2024/05/066865. Participants will be provided with an informed consent form, clearly describing the study’s aim, procedures, risks, benefits, and their right to opt out at any time. Consent for publication of data will be obtained and will be used for all analyses, including secondary analyses. We will confirm that the original consent and institutional review board approval explicitly cover the use of primary and secondary data. We ensure that the data collected will be fully anonymized, with no personally identifiable information retained or linked to any participant. As there are no interventions involved and as only a cross-sectional survey will be conducted in which the data will be collected via an interview and anthropometric measurements, participants will not be provided with any compensation in this study.

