### Data Collection Tools and Methods

Villages from all 8 blocks of Wardha district will be randomly selected using a computer-based randomization method. A list of all children younger than 5 years will be collected from the Anganwadi Center of the respective villages. The children will be selected from the list according to the inclusion and exclusion criteria. The final list of the selected children of respective villages will be arranged according to the location and proximity of their homes, and the investigator will visit their homes for data collection and anthropometric measurements. Data will be collected using a semistructured questionnaire in English/Marathi. The questions will be asked to the informant (either of the parents). The questionnaire will contain questions related to the sociodemographic profile of the child, mother, and household; personal history of the child; livestock ownership; livestock management and disease; environment; and behavioral determinants such as Water, Sanitation, and Hygiene (WASH) (Multimedia Appendix 1). Following the interview, the child’s height and weight will be measured. The digital weighing scale (Seca), pretested for accuracy, will be used to record weight with minimal clothing. Children up to the age of 2 years will have their length measured while lying on the horizontal measuring scale (Seca infantometer). Children older than 2 years will have their height measured with a stadiometer (Prestige). Height measurement will be conducted up to the nearest tenth of a centimeter. The child will have to stand on the scale barefoot, with heels together and shoulder blades, buttocks, and heels touching the vertical surface. The child’s height will be measured by placing a headpiece on the top of their head while they are looking straight ahead and their arms are hanging naturally at their sides. To ensure anthropometric accuracy, the data collectors will undergo 3-day training and standardization sessions following WHO protocols. Technical errors of measurement will be calculated before the study and will be monitored periodically. There will also be regular supervisory visits, which will ensure consistency and interrater reliability. To reduce recall and selection biases, there will be validation assessments utilizing anthropometric data and health records. Moreover, data triangulation will be utilized by combining interviews, focus groups, and observations from the community.

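### The rules for selecting cases and controls are incompatible, and the stated interview-then-measure sequence does not deliver the planned 307 cases and 307 controls

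*Protocol article*

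**What the plan says.** The protocol article gives three accounts of who enters the study.

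- **One sampled control per case.** Study Design, Participants, and Setting: "For each case, 1 control will be recruited through simple random sampling". Sample Size agrees: "The minimal sample size calculated for this study will be 614, of which 307 are cases and 307 are controls". It justifies this equal split by a 1:1 allocation.
- **Every nonstunted child is a control.** The same Study Design section ends: "All stunted children will be the cases in this study, and all nonstunted children will be the controls".
- **Every child in the villages.** Sample Size: "It will include all children younger than 5 years from the respective villages".

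On sequence, Data Collection Tools and Methods has children chosen from the Anganwadi list by the eligibility criteria, then visited at home and interviewed. Only then comes anthropometry: "Following the interview, the child’s height and weight will be measured". The Study Design section assigns stunted or nonstunted status after the measurements have been plotted on the growth charts. It also says that cases and controls will be allocated to blocks in proportion to child numbers and stunting prevalence.

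Sample Size uses a stunting proportion of 28%. The Introduction gives 29.4% for rural Wardha, citing the same reference.

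**The concern.** Who counts as a case or control, and when that becomes known, defines a case-control study. A 1:1 sample needs status before controls are drawn. In the sequence described, status emerges only after the child has been selected and interviewed, and no step for screening or subsampling is given.

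Two field teams following this text could therefore run different studies. One would keep everyone and find far fewer cases than planned. The other would measure many more children than the stated 614 and set aside a large share of the nonstunted. These differ in precision, workload and the analysis set. They also differ in whether stunting prevalence, which the Conclusions promise, can be read directly from the sample: a sample fixed at half stunted cannot give it.

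**Working it through.** **Inputs.** From Sample Size: total 614, split 307/307, p = 0.28, d = 0.05, α = 0.05, N = 88,224. From the Introduction: alternative p = 0.294.

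**1. The plan's own figure.** n = N z² p(1−p) / [d²(N−1) + z² p(1−p)], with z = 1.96.
- z² p(1−p) = 3.8416 × 0.28 × 0.72 = 0.7745
- n = 88,224 × 0.7745 / (0.0025 × 88,223 + 0.7745) = 308.7, so 309

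This is close to 307, and doubled (618) it is close to 614. So 614 is about twice the formula's result, split equally; the split does not come from the formula.

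**2. Can the rules agree?** If all stunted children are cases and all nonstunted children are controls, the ratio of controls to cases is (1−p)/p.
- p = 0.28: 0.72/0.28 = 2.57
- p = 0.294: 0.706/0.294 = 2.40

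A ratio of 1 requires p = 0.50.

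**3. Scenario A: 614 children of unknown status, all kept.**

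| p | Cases = 614p | Controls = 614(1−p) |
|---|---|---|
| 0.28 | 171.9 → 172 | 442.1 → 442 |
| 0.294 | 180.5 → 181 | 433.5 → 433 |

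At p = 0.28 the binomial SD is √(614 × 0.28 × 0.72) = 11.1, giving a 95% range for cases of about 150 to 194, ignoring village clustering. Reaching 307 by chance is not realistic (probability about 10⁻³⁰).

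Approximate SE of the log odds ratio relative to 307/307, √[(1/cases + 1/controls) / (2/307)]:
- 172/442: 1.113
- 181/433: 1.097

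**4. Scenario B: 1:1 governs.** Number to be measured = 307/p; nonstunted children left out = that number − 614.

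| p | Measured | Nonstunted | Left out at 1:1 |
|---|---|---|---|
| 0.28 | 1,096.4 → 1,097 | 790 | 483 |
| 0.294 | 1,044.2 → 1,045 | 738 | 431 |

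If all those nonstunted children were also interviewed and kept, the SE ratio against 307/307 would be 0.833 (307/790) or 0.841 (307/738).

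**5. Detectable odds ratio (illustration only).** The article states neither power nor livestock ownership. Assuming 80% power, two-sided 5%, the two-proportion formula with pooled variance under the null, and no clustering or covariate adjustment:

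| Ownership in controls | 307/307 | 172/442 | 307/790 |
|---|---|---|---|
| 30% | 0.59 | 0.55 | 0.65 |
| 50% | 0.63 | 0.60 | 0.68 |
| 70% | 0.62 | 0.59 | 0.67 |

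**The case against.** The best defence is that the text can be read as a workable 1:1 design. Block allocation implies targets for each group. Stunted and nonstunted children are to be listed separately, and those lists could be the frames from which one control per case is drawn. On that reading, "All stunted children will be the cases in this study, and all nonstunted children will be the controls" labels the groups and sets no sampling fraction, and "It will include all children younger than 5 years from the respective villages" describes the source pool. The article also condenses a fuller protocol in which field sequencing may be spelled out.

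Part of this stands. If 1:1 governs, 307/307 is attainable. The article also does not exclude some provisional knowledge of status at selection, although it describes none and bases status on the study's own measurements. But the charitable reading needs children to be measured before they are selected and interviewed, and the article states the reverse order. The point rests on statements that are present and conflict, not on omitted detail.

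A reader might infer more than the document supports:
- **That the study will yield 172 cases and 442 controls.** This is conditional. It keeps the total of 614 and sets aside the split given in the same sentence.
- **That controls will be stopped ad hoc once a group is full, biasing the village mix.** No such stopping is described, and neither its direction nor its size can be derived.
- **That the ethics text makes this a different design.** "only a cross-sectional survey will be conducted" occurs in an explanation of why participants receive no compensation; it is not a sampling rule.

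**Conclusion.** The point holds as a contradiction in the plan. The stated sequence, at the stated stunting rates, does not give 307/307. Either about 614 children of unknown status are kept and the split is about 172/442 (181/433), with an SE 10–11% larger, or about 1,097 (1,045) are measured to support 1:1 and about 480 (430) nonstunted children are left out.

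The precision loss in the first case is modest, and the odds ratio can be estimated under either scheme. The reason to act is that the sampling rule, the analysis set and the fieldwork volume are not determined by the text.

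The counts assume that stunting among eligible listed children aged 6–59 months equals the planning rate for children under 5. The SE ratios ignore village clustering and covariate adjustment. The detectable odds ratios rest on assumed power and ownership and serve only as illustration.

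**What to change.** State one governing rule and one sequence before data collection, planned from November 2025.

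- **If interview-then-measure stays:** drop the 1:1 quota and analyse every child measured and interviewed. Restate the expected cases and controls and the total to be measured: about 172/442 if the total stays at 614, or about 307/790 from 1,097 children if 307 cases are wanted (181/433, or 307/738 from 1,045, at 29.4%). The first needs only wording. The second adds about 430 to 480 interviews and measurements, and lowers the SE by 16–17% relative to 307/307.
- **If 1:1 stays:** state that measurement precedes selection and interview, and draw controls at random from the nonstunted list. Delete the sentences making all nonstunted children controls and including all children. State the screening number (about 1,045 to 1,097), and adjust for block in the analysis if controls are drawn within block. The cost is real fieldwork: consent and measurement for about 430 to 480 children who will not be interviewed, and either z scores calculated during the visit or a return visit.

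In either case, present any detectable odds ratio as an assumption (80% power) over a range of livestock ownership.
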